### Sample size calculation

The primary aim is to assess the long-term (2 years) effect of a physical activity intervention on SPPB scores. A change of 0.5 points has been defined as a minimum meaningful change in SPPB score and 1 point is considered a substantial change [8, 25]. Based on data from the LIFE and LIFE-P studies, a difference between groups of 0.5 to 0.6 points in change in SPPB scores is feasible at 12 months and at 3 years. In the LIFE study, the standard deviation for the change in SPPB scores from baseline to 2 years was 2.2 and in the OPAL Plus UK-based study the standard deviation for change in SPPB over three years was 2.0 for participants with a baseline SPPB score of 8 or less. We have also assumed a two-sided significance level of 0.05 and that loss to follow-up will accumulate at 12.5% per year throughout the 2-year follow-up period of REACT.

To detect a between-groups difference of 0.5 points in SPPB change scores with a standard deviation of 2.0, with loss to follow-up at 12.5% per year, the required sample size is 384 per arm for 85% power using two sided 5% significance. The REACT study will therefore look to recruit a total sample of 768 participants. This sample size also provides 90% power to detect a difference in moderate intensity physical activity of 50 min per week (standard deviation (SD) 185 min/week) with significance at *p* = 0.05.

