### Randomisation/allocation

When 30 eligible participants have been recruited (enough to form one study group) they will be randomised to one of the two arms (physical activity (intervention) arm or social and education (control) arm using a secure, centralised, web-based randomisation website built by Peninsula Clinical Trials Unit (CTU). Randomisation will be performed using a minimisation algorithm to balance groups in terms of study site (Bath/Bristol, Birmingham, Exeter/Devon), age group, gender and initial functional ability (SPPB score). This algorithm has been built by the Peninsula CTU and uses the method proposed by Taves and extended by Pocock et al. [15, 16]. It maintains a stochastic element by computing probabilities proportional to the existing imbalance at the point of randomisation.

During the pilot phase, the randomisation will be 2:1 (intervention/control) in order to enable feasibility testing of intervention engagement and retention as early as possible. The main trial randomisation will be 1:1. Couples presenting together at the screening where both people are eligible and willing to be involved in the study will be randomised together to reduce contamination between study arms.

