#### Intervention arm

The intervention group will receive a standardised 12-month exercise programme designed for delivery in leisure/community centres where low-cost off-peak capacity is available. REACT will be delivered by qualified exercise professionals with experience of leading exercise classes in the community. We will collaborate with existing community-based organisations who have access to suitable venues and delivery staff. Sessions will be organised as group activities with up to 15 participants per group, but there will be individually tailored elements for aerobic exercise, strength work and exercise progression plans. Activities will include cardiovascular, strength, balance and flexibility exercises and daily lifestyle-based activity in the form of neighbourhood walking and active travel. Breaks in sedentary time will also be promoted. Social activities, such as post-exercise coffee meetings and community-based activities, will be organised to encourage a ‘social club’ atmosphere, promote long-term compliance and contribute to social well-being.

The intervention sets a long-term target for participants of 150 min of moderate-intensity activity per week, which is approached progressively. ‘Home-friendly’ exercises and written materials will be supplied to encourage participation in exercise in the home environment [17]. If participants miss two consecutive sessions, REACT leaders will telephone the participant to problem-solve ways for the participant to re-engage with the programme.

One novel element is the accompanying ‘REACT ambassadors’ scheme that provides the opportunity for participants to develop expertise and contribute as a local neighbourhood coordinator, or in other volunteering roles, determined by the provider. Our aim is to produce a pragmatic model of delivery that is rooted in the needs of the local community, that attracts a diverse population of older adults, is increasingly self-sustaining, and that has potential for application across the UK.

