### Statistical analysis

Primary outcome analysis will be undertaken blinded to group allocation. Primary comparative analyses will be on an intention-to-treat (ITT) basis with due emphasis placed on confidence intervals. Using appropriate descriptive statistics, we will assess any imbalance between the trial arms at baseline and describe the characteristics of participants. The comparison of primary interest is the difference between the intervention and the control arm on SPPB score at the 2-year follow-up. This will be presented as between-group differences in means, 95% CIs and *p* values. Covariates in the model will comprise of baseline SPPB scores, centre, age group and gender.

Depending on the extent of missing primary outcome data, the primary analysis will be repeated using the complete data set generated using multiple imputations. Sensitivity analyses will be conducted to investigate the potential effects of missing data and of any co-interventions on the conclusions.

Secondary outcome analysis will be undertaken using the same general approach as for the primary analysis, using the baseline, 6-month, 1-year and 2-year follow-up data. This will include linear or logistic regression models for continuous or binary outcomes as appropriate.

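### The 384 per arm makes no allowance for clustering by exercise group, and the primary model lists no term for it, so the stated 85% power and the validity of the 95% CI depend on an unstated within-group correlation

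*Protocol article*

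**What the plan says.** The Sample size calculation section of the protocol article gives its full set of inputs. The target is stated as "To detect a between-groups difference of 0.5 points in SPPB change scores with a standard deviation of 2.0". Attrition of 12.5% a year is then allowed for, and the result is that "the required sample size is 384 per arm for 85% power using two sided 5% significance". No ICC, design effect or group size appears there.

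The Intervention arm section says: "Sessions will be organised as group activities with up to 15 participants per group". The programme lasts 12 months, and its sessions are meant to build group identity. The Control arm section offers controls three group sessions over two years.

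The Randomisation/allocation section describes individual randomisation by minimisation once 30 eligible people have been recruited. It makes one exception: "Couples presenting together at the screening where both people are eligible and willing to be involved in the study will be randomised together".

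The Statistical analysis section sets the primary comparison at the 2-year follow-up and says: "Covariates in the model will comprise of baseline SPPB scores, centre, age group and gender". Secondary outcomes follow the same general approach, with linear or logistic regression. The sensitivity analyses named there concern missing data and co-interventions, not clustering.

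**The concern.** Intervention participants share a trainer, a venue and a peer group for a year, and group cohesion is part of how the programme is meant to work. Some similarity of outcome within exercise groups is therefore plausible. Controls have no comparable shared exposure, so the design is partially nested: clustered in one arm and close to independent in the other.

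If that correlation exists and is ignored, the standard error of the primary contrast is understated. The confidence interval, to which the plan gives particular weight, would then be too narrow and the test would reject too often. Separately, the 85% power is published without conditions although its derivation assumes independence. Centre has only three levels and cannot stand in for about 26 exercise groups (384/15 = 25.6).

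**Working it through.** **Inputs from the protocol article.** From Sample size calculation: difference 0.5, SD 2.0, two-sided 5%, power 85%, loss 12.5% per year (25% over two years if added). From Randomisation/allocation: "The main trial randomisation will be 1:1", and batches of 30. From Intervention arm: groups of up to 15.

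**Step 1: reproduce the plan's figure.** n per arm = 2(1.960 + 1.036)² × (2.0/0.5)² = 287.3, so 288 evaluable. Then 288/(1 − 0.25) = 384 exactly. Compounding the loss (1 − 0.875² = 23.4%) gives 377. With 288 per arm, SE = 2.0 × √(2/288) = 0.1667, 0.5/0.1667 = 3.00, and power = Φ(3.00 − 1.96) = 85.1%. The figure reproduces with no design effect.

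**Step 2: add clustering in the intervention arm only.** The ICC ρ is an assumption, because the article gives none. Group size m is 15, or 15 × 0.75 = 11.25 after loss.

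- Design effect: DE = 1 + (m − 1)ρ
- True SE = 2.0 × √((DE + 1)/288)
- Power = Φ(0.5/SE − 1.96)
- Type I error of the unadjusted test = 2[1 − Φ(1.96 × 0.1667/SE)]

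Worked case, m = 15 and ρ = 0.02: DE = 1.28, SE = 2.0 × √(2.28/288) = 0.178, power = Φ(2.81 − 1.96) = 80.2%, type I error = 2[1 − Φ(1.836)] = 6.6%.

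| ICC | m | DE | True SE / naive SE | Type I error | Power |
|---|---|---|---|---|---|
| 0.01 | 11.25 | 1.10 | 1.03 | 5.6% | 83.3% |
| 0.01 | 15 | 1.14 | 1.03 | 5.8% | 82.6% |
| 0.02 | 11.25 | 1.21 | 1.05 | 6.2% | 81.5% |
| 0.02 | 15 | 1.28 | 1.07 | 6.6% | 80.2% |
| 0.05 | 11.25 | 1.51 | 1.12 | 8.0% | 76.3% |
| 0.05 | 15 | 1.70 | 1.16 | 9.2% | 73.3% |

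**Step 3: correlation shared with controls.** Each batch of 30 supplies both arms. A batch or area effect common to both therefore largely cancels in the contrast, and only the part specific to the exercise group inflates the error. A simulation with 26 batches, 11 completers per arm per batch and total within-group ICC 0.05 gave unadjusted type I error of 7.9% if none of the correlation is shared with batch controls, 6.3% if half is, and 4.9% if four-fifths is. The split is an assumption. Step 2 is thus the case in which nothing is shared.

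**Step 4: baseline adjustment.** The plan sizes on the SD of change but adjusts for baseline SPPB. If the residual SD were 1.9 (assumption) with m = 11.25, power would be 86.9%, 85.3% and 80.4% at ICC 0.01, 0.02 and 0.05. The type I error does not change, because the ratio of true to naive SE does not depend on the SD.

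**Step 5: couples.** With 5–20% of participants in pairs and a within-pair correlation of 0.1–0.3 (assumptions), DE = 1 + fraction × correlation runs from 1.005 to 1.06 in both arms. Power for couples alone runs from 84.9% to 83.0%.

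**The case against.** A reader might infer that the trial's error bars are too narrow as a matter of fact. The documents do not support that. The article lists covariates; it does not state the variance structure or rule out a random effect or robust standard errors. The SAP is not shown, and such detail is commonly left to it.

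The size is also uncertain. No ICC is given, and at 0.01 the effect is small. The outcome is measured 12 months after the programme ends, when continued sessions are optional and groups organise themselves, so correlation may have faded. Step 3 shows that correlation shared with batch controls largely cancels. All of this stands, and it is why the inferential part of the point is conditional.

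A second tempting reading is that 85% power is unattainable unless the ICC is zero. That is true only on the plan's stated inputs. If baseline adjustment brought the residual SD to 1.9, about 85% would be kept at ICC 0.02. That reduction is not assured: the same section also reports an SD of 2.2 for two-year change in the larger US trial.

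These objections leave two things untouched. A random effect in the SAP would correct the interval but not the unconditional power published here, whose derivation is fully visible. Baseline adjustment can offset lost power but cannot correct an understated standard error.

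**Conclusion.** The point holds in conditional form. It is established that 384 per arm rests on independent observations, with no margin for clustering, and that the listed primary-model terms include none for exercise group or couple. It is not established that the eventual confidence interval will be too narrow. That requires a positive 24-month correlation specific to exercise groups, beyond what batch controls share, and an analysis that ignores it.

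Under those conditions, across the assumed ICC range of 0.01 to 0.05, the cost runs from slight (type I error 5.6–5.8%, power about 83%) to material (8.0–9.2%, 73–76%). It begins to matter from an ICC of about 0.02. These figures take 1:1 allocation, 288 evaluable per arm and no credit for baseline adjustment. Couples are a minor contributor. The result does not show that the trial is too small or that more participants are needed.

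**What to change.** **Statistical analysis section.** For the primary model, and for secondary outcomes using the same approach, specify a partially nested mixed model with:

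- a random exercise-group effect in the intervention arm;
- allowance for the recruitment batch shared by both arms, so that batch variance is not attributed to the intervention arm;
- a small-sample degrees-of-freedom correction, given about 26 groups.

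Add a cluster-robust check that covers couples. If the SAP already provides this, cite the place instead.

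**Sample size calculation section.** Replace the unconditional 85% with power conditional on a stated ICC and group size, for example about 80–82% at ICC 0.02 and 73–76% at 0.05 on the current inputs. Any credit taken for baseline adjustment should be stated with its assumed residual SD. Do not enrol more.

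**Cost.** Analysis wording and one restated figure. The downside is a slightly wider confidence interval and a less favourable stated power.

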### Statistical analysis

Primary outcome analysis will be undertaken blinded to group allocation. Primary comparative analyses will be on an intention-to-treat (ITT) basis with due emphasis placed on confidence intervals. Using appropriate descriptive statistics, we will assess any imbalance between the trial arms at baseline and describe the characteristics of participants. The comparison of primary interest is the difference between the intervention and the control arm on SPPB score at the 2-year follow-up. This will be presented as between-group differences in means, 95% CIs and *p* values. Covariates in the model will comprise of baseline SPPB scores, centre, age group and gender.

Depending on the extent of missing primary outcome data, the primary analysis will be repeated using the complete data set generated using multiple imputations. Sensitivity analyses will be conducted to investigate the potential effects of missing data and of any co-interventions on the conclusions.

Secondary outcome analysis will be undertaken using the same general approach as for the primary analysis, using the baseline, 6-month, 1-year and 2-year follow-up data. This will include linear or logistic regression models for continuous or binary outcomes as appropriate.

#### Subgroup analyses

We will compare the primary outcome between sub-groups characterised by: (1) high vs. low adherence; (2) co-morbidity levels (one or less known chronic medical conditions vs. multiple co-morbidities); (3) socio-economic subgroups (using education, housing type and postcode), age categories (65–74 years and 75 + years); (4) gender and REACT site (Bath/Bristol, Devon, Birmingham) and (5) fallers and non-fallers (in 6 months prior to baseline).

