#### Control arm

After completion of baseline assessments, participants allocated to the control group will be given information regarding healthy ageing. They will be invited to three 60–90-min group sessions over the 2 years of the study. These will consist of presentations and discussion groups on various aspects of healthy ageing (excluding physical activity) and incorporate socialising opportunities.

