### Assessments

A full list of measures and time points is presented in Table 2. The person conducting the assessments will check for completion of questionnaires before participants leave the assessment premises, and will make every effort to ensure that missed or spoiled questions are addressed.

**Table 2 Tab2:** REACT schedule of assessment

Visit type	Scr1^1^	Scr2^2^	FU3^3^	FU4^4^	FU5^5^
Visit code		SV1	F06	F12	F24
Visit number		1	2	3	4
Telephone call	1				
Activity/assessment month	− 0.5	0	6	12	24
Form name					
Verbal consent	X				
Telephone screening (some elements of inclusion and exclusion criteria) (see Additional file 4)	X				
Written informed consent (see Additional file 5)		X			
Contact information update	X	X	X	X	X
Demographic, social, economic	X				
SPPB battery (see Additional file 6 for full CRF) [12]		X	X	X	X
Accelerometry		X	X	X	X
Height and weight		X		X	X
MoCA – Montreal Cognitive Assessment [13]		X	X	X	X
PASE questionnaire [14]		X	X	X	X
Dynometer (hand-grip strength)		X	X	X	X
Ageing Well profile (two sites full scale, one site social well-being scale only) [15]		X		X	X
Health-related quality of life (EQ-5D-5 L, SF-36) [16, 17]		X	X	X	X
Sleep Condition Indicator [18]		X		X	X
Pain (Western Ontario and McMaster Universities Osteoarthritis Index (WOMAC) [19]		X		X	X
Mobility Assessment Tool-short form (MAT-sf) [20]		X	X	X	X
Cognitive function (UK Biobank Healthy Minds Questionnaire) [21]		X	X	X	X
Medical history including medications, chronic diseases, cardiovascular disease and other conditions		X			
Falls Inventory including falls in last 6 months and injuries relating to falls		X	X	X	X
Health and Social Service Usage including use of primary, secondary or community care services in previous 6 months		X	X	X	X
*(MRI sub-study)* MRI scan, detailed cognitive assessment and gait analysis		X	X	X	
Process evaluation^6^			X	X	
Session attendance (intervention group only)			X	X	
Total contact time for each participant		X	X	X	
Physical activity related self-concept			X	X	X
Perceived tension of maintaining current PA			X	X	X
Perceived tension of maintaining current exercise		X	X	X	X
Autonomy in relation to PA		X	X	X	X
Competence for PA		X	X	X	X
Relatedness for PA		X	X	X	X
Enjoyment of PA		X	X	X	X
Perceived intrinsic benefits of PA (social, physical and emotional)					
Autonomy for strength-building exercise		X	X	X	X
Competence for strength-building exercise		X	X	X	X
Relatedness for strength-building exercise		X	X	X	X

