#### Subgroup analyses

We will compare response to exercise based on SPPB score (ranges 4–7 and 8–9), adherence (high-low), age categories (65–74, 75 + years), gender and cognition (MoCA < 26 > 26, 26 + years).

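### High versus low adherence is listed as a subgroup factor for the primary outcome and the MRI sub-study, but it arises after randomisation and has no comparable control group, so the comparison mixes selection with effect

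*Protocol article*

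**What the plan says.** The Subgroup analyses paragraph under Statistical analysis opens with "We will compare the primary outcome between sub-groups characterised by: (1) high vs. low adherence". The remaining factors are co-morbidity, socio-economic measures, age category, gender, site, and falls in the six months before baseline. All of these describe the participant at entry, and Table 2 schedules demographic and social data and medical history only at screening or baseline.

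The subgroup paragraph of the MRI imaging sub-study again names "adherence (high-low" as a factor, beside SPPB range, age, gender and cognition.

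Adherence is not defined in the article. In Table 2 (Assessments) the only attendance row is "Session attendance (intervention group only", marked at months 6 and 12. A separate row, "Total contact time for each participant", is not restricted to one arm.

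On exposure, "The intervention group will receive a standardised 12-month exercise programme", whereas for controls "They will be invited to three 60–90-min group sessions over the 2 years of the study", with physical activity excluded from the content.

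The main analysis is clear: "The comparison of primary interest is the difference between the intervention and the control arm on SPPB score at the 2-year follow-up", and "Primary comparative analyses will be on an intention-to-treat (ITT) basis". The model covariates are baseline SPPB, centre, age group and gender.

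**The concern.** A subgroup analysis in a randomised trial compares the arms within levels of a factor that allocation cannot influence. Adherence to a programme is not such a factor. It is observed after allocation, and the control arm offers nothing equivalent, so there is no set of controls who would have been high adherers to set against the observed ones. Only two comparisons remain: high against low adherers within the intervention arm, or each of these against all controls. Neither is a randomised contrast.

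The population makes confounding plausible. Participants enter with SPPB 4 to 9 and are at risk of further decline. Someone who becomes ill or loses mobility during the first year may both attend less and score lower at 24 months, whether or not the programme works.

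What is at stake is interpretation. After a null ITT result, a high-low difference could be taken to mean that the programme works for those who attend; after a positive one, it could be taken as a dose-response.

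**Working it through.** **1. The plan's own figure.** Inputs from Sample size calculation: difference 0.5, SD 2.0, two-sided 5%, power 85%, loss of 12.5% per year for two years.

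- Evaluable per arm: 2 × (1.960 + 1.036)² × 2.0² / 0.5² = 287.3, rounded up to 288.
- With 25% loss: 288 / 0.75 = 384 per arm, as stated.

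The sample size is not in question. It supplies the SD, the target difference and the 288 evaluable per arm used below.

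**2. Timing and arm of the factor.** The programme lasts 12 months and attendance is recorded at months 6 and 12, so adherence is known only after randomisation. The attendance row covers the intervention group only. The contact-time row is open to both arms, but three control sessions over two years cannot yield a high-low split comparable with one from a programme of weekly or twice-weekly sessions.

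**3. Size of the selection bias under no effect.** Let r be the correlation between attendance and 24-month SPPB change that remains after adjustment for the model covariates. The documents give no value for r, so a range is shown. Attendance and SPPB change are taken as bivariate normal, the intervention arm is split at median attendance, and the SD of 2.0 is kept.

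- High minus low: 2 × √(2/π) × r × SD = 2 × 0.798 × r × 2.0 = 3.19 × r.
- High minus all controls: half of that, 1.60 × r.

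The rejection rates come from 4,000 simulated trials per row with a true effect of zero, 288 evaluable per arm and a t test:

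| r (assumed) | High − low, points | p < 0.05 | High − all controls, points | p < 0.05 |
|---|---|---|---|---|
| 0 | 0.00 | 5% | 0.00 | 5% |
| 0.1 | 0.32 | 27% | 0.16 | 13% |
| 0.2 | 0.64 | 78% | 0.32 | 34% |
| 0.3 | 0.96 | 99% | 0.48 | 65% |
| 0.4 | 1.28 | 100% | 0.64 | 89% |

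**4. Correlation that mimics the target.** 0.5 / 3.19 = 0.157, so r of about 0.16 gives a high-low difference equal to the 0.5 points that the protocol takes as the minimum meaningful change.

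**The case against.** *The size is assumed.* This stands. No passage says that attenders are healthier, and everything in the table depends on r. Restricting entry to SPPB 4 to 9 and adjusting for baseline SPPB, centre, age group and gender would absorb part of any link between attendance and function. For that reason r must be read as the correlation left after adjustment, and the figures must not be presented as the bias of the planned analysis. Adjustment cannot, however, reach illness or loss of mobility that occurs after baseline and affects both attendance and outcome.

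*Adherence is undefined, and a statistical analysis plan may define it.* This stands in part. That adherence is measured only in the intervention arm is an inference from the attendance row, not a statement in the subgroup paragraph. But a definition or cut-off would not make a post-randomisation variable a baseline one or create comparable controls. The fault lies in the classification, which the article itself fixes.

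*The trial team may not intend a causal reading.* This is fair. The ITT contrast is named as the comparison of primary interest, and the Process evaluation section treats adherence data as something to be interpreted in context. Still, the subgroup paragraphs place adherence beside true baseline subgroups with no caveat.

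A reader might infer that the analysis is almost certain to favour attenders. The documents do not support this: at r = 0.1 only about 27% of null trials would show a significant high-low difference.

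**Conclusion.** The point holds. Adherence is wrongly classed as a subgroup factor in two places, and the resulting comparison has no randomised basis whatever cut-off is used. With SD 2.0, a median split and no true effect, a modest residual correlation of 0.1 to 0.3 would produce a spurious high-low difference of 0.32 to 0.96 points against a target of 0.5. These sizes are illustrative. They rest on an assumed r, on approximate normality, and on healthier participants attending more; if the sickest or most worried attended more, the sign would reverse.

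A reader might go further and conclude that the trial's main result is compromised. It is not: the primary ITT comparison and the 384 per arm do not depend on adherence. The consequence is confined to the subgroup analysis of the primary outcome and its counterpart in the MRI sub-study. The change should be made, but the validity of the trial does not turn on it.

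**What to change.** Remove adherence from the subgroup lists under Statistical analysis and under the MRI imaging sub-study. Present outcome by level of attendance in the intervention arm as descriptive, and state that it is non-causal.

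If the effect of attending is of interest, add a supportive instrumental-variable analysis with randomised arm as the instrument and the primary-model covariates. Choose one exposure in advance:

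- sessions attended as a continuous dose; or
- a complier average causal effect with a pre-defined attendance threshold.

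State the exclusion restriction, namely that allocation affects SPPB only through the chosen exposure. With a threshold, this also requires that attendance below it has no effect, which is doubtful if partial attenders benefit. The continuous dose eases that problem but assumes a form for the dose-response. The instrumental-variable analysis is optional; reclassifying adherence is not.

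The cost is new wording in two paragraphs and, if wanted, one extra analysis of data already scheduled for collection. The complier estimate will have a wider interval than the ITT estimate.
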